#### Prognostic value of variables

Depending on normality of data the Pearson or Spearman correlation coefficients will be used to assess correlations. A scatterplot for numerical data and Odds Ratio (OR) for binary data will be used to provide additional information on possible correlations in the data between prognostic factors. In case of correlations (*p* < 0.10 to avoid overfitting [40]) shown by an univariate analysis, a multivariate logistic regression will be performed to assess dependency between variables. The R^2^ will be used to visualize model fitness for the contribution of a factor to the progression to CAI and for the full model.

#### Prognostic model

For internal validation a maximal amount of data is required to increase the reliability, therefore apparent validation will be used, including the full sample size of 1026 patients. To increase reliability the bootstrapping procedure will be used in the development of the model. A sample of 1000 bootstraps will be used to assess bias in the regression coefficients. Additionally the sensitivity, specificity and ROC curve will be used to assess the predictive value of the model.

To define generalizability of the created model, temporal validation is chosen to decide whether patients will be included in the internal or external validation database. After determining the prognostic value of the included variables, the full required sample size is calculated. Additionally the duration until this sample size will be reached, is estimated. Subsequently the time stamp for the temporal validation is decided. This ensures both sample sizes will be sufficient and reached. Again the sensitivity, specificity and ROC curve will be used to assess the suitability of the model [36].

Variables with a significant correlation with CAI (age, sex, height, BMI, sports intensity, varus/valgus alignment, fibular position, tibiotalar contact ratio, height medial malleolus and talar convexity), in addition to a continuous model, will be categorized to provide a binary model that can be easily implemented in daily practice by simply answering question by ‘yes’ or ‘no’. For this the Youden index and a ROC curve will be used [33]. For both models the final objective is to create a model with cut-off values that advises surgery, watchful waiting or no surgical treatment by combining the scores with the patients expectations in the shared decision making process.

The cut-off values will be reflected to the MDC, SEM and MCID to ensure minimal measurement bias.

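### Internal validation is by apparent performance with the bootstrap aimed at coefficients, so internal AUC, sensitivity and specificity will be optimistic; separately, no calibration measure is named for either validation set

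*Protocol article*

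**What the plan says.** All of this stands in the protocol article, Data analysis and statistics, Prognostic model, unless another section is named.

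- Internal validation: "For internal validation a maximal amount of data is required to increase the reliability, therefore apparent validation will be used". The sample size named for this step is 1026.
- Bootstrap: "To increase reliability the bootstrapping procedure will be used in the development of the model", and then its one stated target: "A sample of 1000 bootstraps will be used to assess bias in the regression coefficients".
- Internal performance: "Additionally the sensitivity, specificity and ROC curve will be used to assess the predictive value of the model".
- External validation: "temporal validation is chosen to decide whether patients will be included in the internal or external validation database". Performance there: "Again the sensitivity, specificity and ROC curve will be used to assess the suitability of the model".
- Yes/no model: predictors that correlate significantly with chronic ankle instability (CAI) are also dichotomised, alongside the continuous model. "For this the Youden index and a ROC curve will be used". The data set for this search is not named.
- Screening (Prognostic value of variables): univariable p < 0.10, then multivariable logistic regression; R² is the only other measure of fit. The section Assessment of agreement places this work in the internal validation sample.
- Size (PREDICT sample size, Table 2): 16 variables, 20 events per variable, 30–40% CAI and 10% loss, giving 1185 patients for internal and 1185 for external validation.

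**The concern.** Apparent performance is measured on the patients who chose the predictors and set the coefficients, so it describes fit and does not validate the model. The reason given, to use as much data as possible, argues against splitting the sample. It does not argue for apparent validation, because bootstrap optimism correction also uses every patient. The resamples are already planned but are pointed at the coefficients.

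Two things are at stake. The internal figures will be too favourable, more so for the yes/no version if its cut-points are searched in the same patients. Second, and separately, the product is a risk model whose cut-offs are to feed advice on treatment, yet no stated measure compares predicted with observed risk in either set.

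**Working it through.** **1. Development sample.** Events needed: 20 × 16 = 320. At 30% CAI: 320/0.30 = 1067 evaluable (the plan's factor gives 320 × 3.33 = 1065.6). With 10% loss: 1067/0.9 ≈ 1185. The plan's figure is reproduced, so the check uses n = 1066. The 1026 in the Prognostic model section does not follow from 16 variables; it equals 14 × 20 × 3.33 × 1.1 = 1025.6. That is a separate inconsistency and hardly affects this point (step 3).

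**2. Simulation.** From the plan: 16 candidates, 30% events, p < 0.10 univariable screen, logistic model, Youden cut per predictor for the yes/no model. Assumed, because the article gives no effect sizes: independent normal predictors, the signal strengths below, and the cut-point search in the development data. There were 100 data sets per scenario (85 usable with no signal); the truth was taken from 20,000 new patients. Optimism = apparent AUC − AUC in new patients, from unrounded values. SD is that of the true linear predictor.

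| Signal (SD) | Continuous: apparent / new | Optimism | Slope | Yes/no: apparent / new | Optimism | Slope |
|---|---|---|---|---|---|---|
| 5 predictors (0.4) | 0.621 / 0.587 | 0.034 | 0.72 | 0.641 / 0.566 | 0.075 | 0.46 |
| 10 predictors (0.6) | 0.665 / 0.633 | 0.033 | 0.79 | 0.688 / 0.603 | 0.085 | 0.53 |
| 5 predictors (0.8) | 0.709 / 0.693 | 0.016 | 0.91 | 0.706 / 0.651 | 0.055 | 0.71 |
| none | 0.557 / 0.500 | 0.057 | 0.00 | 0.571 / 0.500 | 0.071 | 0.00 |

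Sensitivity and specificity need a cut-off on the model score. With that cut-off also chosen by Youden in the development data (an assumption), sensitivity + specificity − 1 is too high by 0.048–0.077 for the continuous model and 0.098–0.144 for the yes/no model in the three scenarios with signal.

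**3. Sensitivity to n.** At n = 1026 the same three scenarios give AUC optimism of 0.036, 0.030 and 0.012 (continuous) and 0.077, 0.085 and 0.054 (yes/no).

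**4. Does the repair work?** A further run used 60 data sets at n = 1066, with 4 of 16 predictors at an assumed odds ratio of 1.3 per SD. Continuous: apparent 0.653, new patients 0.635. Yes/no: apparent 0.657, new patients 0.603. Bootstrap correction that repeated screening and cut-point search in each resample gave 0.629 and 0.601, both close to the truth.

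**5. Calibration.** AUC depends only on the ordering of patients. Sensitivity and specificity count classified patients. None of them compares a predicted risk with an observed frequency. Illustration with slope 0.53, taking 30% as the pivot: a predicted risk of 60% has logit 0.405; the logit of 30% is −0.847; the difference is 1.253. The actual logit is −0.847 + 0.53 × 1.253 = −0.183, a risk of about 45%. The ROC curve is the same whether 60% or 45% is reported.

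**The case against.** The strongest objection is the temporal validation. A reader might infer that all reported performance will be too good. The article does not support that: 1185 later patients are planned, and results there carry no development optimism if coefficients and cut-offs are fixed beforehand. This stands and limits the optimism point to the internal results. The article does not, however, say that the model is frozen first.

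Other parts also stand:

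- Missing calibration does not inflate AUC, sensitivity or specificity. It is a separate gap in detection.
- That Youden is applied to the development data is an inference. The article describes only an internal and an external database, and a search in the external one would compromise the external validation instead.
- The yes/no figures are somewhat high. Sex is already binary, the varus/normal/valgus categories have preset limits, and unreliable or collinear variables will be dropped, so fewer than 16 cut-points would be searched.
- At 20 events per variable the optimism of the continuous model is modest. Larger values at about 533 patients would belong to the stage that assesses variables at 10 events per variable, not to the prediction model.

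A reader might also infer that Youden sets the cut-offs for the three-way treatment advice, or that the plan will prefer the yes/no model for its apparent AUC. Neither is supported. Youden is attached to categorising the predictors, and the yes/no model is offered in addition to the continuous one, with no rule for choosing between them.

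The objection that a fuller document may supply the detail does not remove the point. The article names its internal method, the target of its bootstrap and its performance measures; the difficulty lies in what it names. Its general remark that bootstrapping serves model development does not mention performance.

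**Conclusion.** The point holds for the internal results. As written, internal AUC will be too high by about 0.02–0.03 for the continuous model. For the yes/no model the excess is about 0.055–0.085 if cut-points are searched in the development data, and somewhat less where predictors need no search. These sizes rest on assumed signal strengths and independent predictors. The direction was the same in every scenario run, including no signal at all, where continuous AUC optimism was about 0.06.

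Separately, neither validation as described would detect miscalibrated risks. Slopes in new patients of 0.72–0.91 (continuous) and 0.46–0.71 (yes/no) in the scenarios with signal show that this is a realistic possibility. Discrimination in the temporal set is not affected, provided that the model is frozen first.

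**What to change.** 1. Replace apparent validation by bootstrap optimism correction on the full development sample, with the 1000 resamples already planned. Repeat the p < 0.10 screen, the variable selection and the Youden cut-point search in each resample.
2. Report optimism-corrected AUC, sensitivity, specificity and calibration slope, for the continuous and the yes/no model.
3. State that cut-points are derived in the development data, and that coefficients and cut-offs are frozen before the temporal set is analysed.
4. In the temporal set, report calibration intercept, slope and plot beside sensitivity, specificity and the ROC curve.

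The yes/no tool can stay as planned. No extra patients, visits or measurements are needed. The cost is slightly more analysis work and less favourable internal figures.

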**Methods:**

In this observational prospective cohort, all patients aged sixteen years and older, reporting at the emergency department of one of the participating hospitals after sustaining a lateral ankle sprain, and filled out 1 out of 3 follow-up questionnaires and the 1 year follow-up are included. A lateral and anteroposterior radiograph is made. Patients are excluded if a fracture or other pathology is present. The included patients receive four questionnaires, including questions focusing on the sprain, treatment and complaints, the Foot and Ankle Outcome Score and the Cumberland Ankle Instability Tool. A total of eleven radiographic variables are assessed for inter- and intra-observer reliability. Additionally, four factors extracted from the questionnaires, will be evaluated for correlation with CAI. Significantly correlating factors (e.a. risk factors) will be implemented in a risk assessment model. For the final model, based on sixteen variables with a minimum of 20 events per variable and a prevalence of 30–40% after an initial sprain, a sample size of 2370 patients is needed to perform both internal and external model validation.

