### Clinical outcome measures

The first outcome measure is the radiograph made at the ER. This radiograph will be assessed for nine bone geometric characteristics. These characteristics will be implemented in the model in case they show a correlation with developing CAI: ankle alignment using the medial distal tibial angle (MDTA) measured as (1) the absolute angle and whether this angle was considered a (2) varus (<87^o^), normal (87-91^o^) or valgus (>91^o^) position [27], fibular position in relation to the tibia measured as (3) projected distance and (4) relative distance [28], and tibiotalar contact ratio assessing the (5) talar height, (6) radius and (7) angle between the talus and tibia, (8) the angle representing the height of the medial malleolus and (9) the talar curvature (Figs. 2, 3 and 4) [29]. Additionally (10) the Medial Malleolar Height Angle (MMHA) and (11) the Talar Convexity Angle (TCA) [30] (Figs. 5 and 6).

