#### Prognostic model

The main objective of this study is to assemble the required data and subsequently construct a risk assessment model for the development of CAI after a first initial ankle sprain based on patient characteristics and the ankle joint geometric characteristics. This model is based on fourteen factors that are assessed using a mortise view and lateral radiographs and a questionnaire. The patient characteristics that are implemented in the model are age, sex, height, BMI and sports intensity. Even though BMI and sports intensity may be considered as modifiable, BMI reflects the current situation and sports intensity is the level a patient wishes to return to, additionally reflecting the risk at ankle sprain exposure. Additionally nine bone geometric characteristics are implemented in the model (See clinical outcome measures).

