#### Assessment of agreement

Assessment of the prognostic value of the fourteen variables will be performed on the sample size of the internal validation [36]. To avoid overfitting, the prognostic value of these 16 variables will be assessed when 10 events per variable (EPV) is reached [37]. With a maximum of sixteen variables with a minimum of 10 events per variable, a prevalence of 30–40% after an initial sprain, including a 10% loss-to-follow-up, a sample size of 593 patients is needed to assess their prognostic value (Table 2).

**Table 2 Tab2:** Sample Size calculation prognostic value, internal validation [38, 39]

EPV = no. of events/no. of regression coefficients		
Minimal EPV	≥10 Prognostic Value	≥20 Prediction Model
Change of developing CAI	30–40%	30–40%
No. of regression coefficients	16	16
(? = no of events needed)	10 =?/16 ? = 160 minimal 160 events	20 =?/16 ? = 320 → minimal 320 events
In case of 30% chance of developing CAI	160*3.33 = 532.8 patients	320*3.33 = 1065.6 patients
In case of 40% chance of developing CAI	160*2.5 = 400 patients	320*2.5 = 800 patients
Sample Size (incl. 10% loss to follow-up)	445–593 patients	889–1185 patients

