#### PREDICT sample size

For a prognostic model at least 20 EPV is needed to optimize reliability and to avoid bias in regression coefficients [37–39]. Based on having maximally 16 variables with a minimum of 20 events per variable, a prevalence of 30–40% after an initial sprain, including a 10% loss-to-follow-up, a sample size of 1185 patients is needed to perform the internal and 1185 patients is needed to perform the external model validation, resulting in a total of 2370 patients (Table 2).

During the study the required sample size may change and will be recalculated accordingly in case one of the following scenarios occur:In case one or more radiographic factors have a low inter- or intra-observer reliability (ICC ≤0.70), they will be excluded from the risk assessment model and the sample size will be recalculated using the new number of prognostic factors. If radiographic assessments cannot be performed in more than 2 cases (> 5%) a candidate predictor will be excluded, as the problem is likely to recur and therefore cannot be adequately assessed, now and during future assessment (e.g. up to 5% missing data is accepted) [40, 41].In case of multicollinearity between (ICC > 0.70) between prognostic variables one will be excluded;If a variable lacks agreement (ICC ≤0.70) with CAI it will be excluded;In case the prevalence of CAI during the study differs from the estimated 30%. In case the percentage of patients progressing to CAI exceeds the 50%, the sample size calculation will be based on the number of non-events. The prevalence will be recalculated when 500, 750, 1000, 1250, 1500, 1750,2000 and 2250 patients have returned the last questionnaire to minimize patient burden, as inclusion will stop as soon as the minimal required sample size is reached.

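### The model-analysis section gives 1026 patients for internal validation where the sample-size section requires 1185, and the number of candidate predictors is not consistent across the protocol

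*Protocol article*

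**What the plan says.** **Sample size.** The PREDICT sample size section plans as follows: "Based on having maximally 16 variables with a minimum of 20 events per variable". With a prevalence of 30–40% and 10% loss to follow-up it concludes that "a sample size of 1185 patients is needed to perform the internal and 1185 patients is needed to perform the external model validation", 2370 in total. Table 2 (under Assessment of agreement) sets "minimal 320 events" for the prediction model and defines EPV as events divided by the number of regression coefficients. The abstract repeats sixteen variables and 2370.

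**Analysis.** The Prognostic model section under Data analysis and statistics says that "apparent validation will be used, including the full sample size of 1026 patients". It does not derive the figure or describe it as recalculated.

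**Number of predictors.**
- Prognostic model section under Analyses: "This model is based on fourteen factors that are assessed using a mortise view and lateral radiographs and a questionnaire", made up of five patient characteristics and nine geometric ones.
- Assessment of agreement: "Assessment of the prognostic value of the fourteen variables will be performed on the sample size of the internal validation". The next sentence speaks of 16 variables.
- Clinical outcome measures: "This radiograph will be assessed for nine bone geometric characteristics". The list that follows numbers eleven radiographic items and then five patient characteristics, up to (16).
- Abstract: eleven radiographic variables, and "four factors extracted from the questionnaires, will be evaluated for correlation with CAI". The body lists five.

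**The concern.** Two sections give different sizes for the same analysis set, the one on which the main objective rests. A reader carrying out the analysis section would work with 1026 patients, and a reader of the sample-size section with 1185. If 1026 were used with sixteen predictors, the plan's own minimum of 20 EPV could be missed. That criterion is its stated protection against biased coefficients.

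The predictor count matters for the same reason. The required number of events is 20 times that count, and every planned recalculation starts from it. A protocol that gives it as both fourteen and sixteen leaves the starting point open.

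**Working it through.** **Inputs.** 16 predictors, 20 EPV, prevalence 30–40% and 10% loss (PREDICT sample size, Table 2). The same section calls 30% the estimated prevalence, and 30% is what produces 1185. Table 2 uses a multiplier of 3.33 for 30%. The figure 1026 is from the Prognostic model section under Data analysis and statistics.

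**1. The plan's own figure.** N = (EPV × predictors ÷ prevalence) ÷ (1 − loss).
- Events: 20 × 16 = 320.
- 320 ÷ 0.30 = 1066.7; ÷ 0.9 = 1185.2. The stated 1185 reproduces (strict rounding up would give 1186).
- The other Table 2 totals reproduce too: 160 ÷ 0.30 ÷ 0.9 = 592.6 (593 stated); 400 ÷ 0.9 = 444.4 (445); 800 ÷ 0.9 = 888.9 (889).

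**2. Can 16 predictors give 1026 at 30%?**
- Before loss: 1066.7, or 1065.6 with 3.33.
- Loss by division by 0.9: 1185.2, or 1184.0 with 3.33.
- Loss by multiplication by 1.1: 1173.3, or 1172.2 with 3.33.
- Analysable part of 1185: 1185 × 0.9 = 1066.5.

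None gives 1026.

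**3. Can 14 predictors give it?**
- 14 × 20 = 280; 280 × 3.33 = 932.4; × 1.1 = 1025.6, which rounds to 1026.
- With Table 2's division by 0.9: 932.4 ÷ 0.9 = 1036.0.

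The match is to the unit, but only with a different allowance for loss from the one in Table 2.

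**4. What 1026 delivers for 16 coefficients.** EPV = N × (1 − loss) × prevalence ÷ 16. The article does not say whether 1026 is before or after loss, so both readings are shown.

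| Prevalence | 10% lost: EPV | None lost: EPV |
|---|---|---|
| 30% | 17.3 (277.0 events) | 19.2 (307.8 events) |
| 35% | 20.2 | 22.4 |
| 40% | 23.1 | 25.7 |

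Prevalence needed for 320 events: 320 ÷ (1026 × 0.9) = 34.7%, or 320 ÷ 1026 = 31.2%. For comparison, 1185 × 0.9 × 0.30 = 319.9 events, or 20.0 EPV.

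**5. How far the count moves N** (30%, division by 0.9, rounded up).
- 14 coefficients: 280 ÷ 0.30 ÷ 0.9 = 1037.04, so 1038 per phase.
- 16 coefficients: 1186 (1185 as stated).
- 17 coefficients: 340 ÷ 0.30 ÷ 0.9 = 1259.3, so 1260.

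Seventeen arises if all sixteen items are entered and the varus/normal/valgus class of the medial distal tibial angle (MDTA) takes the two coefficients that a three-level factor needs.

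**The case against.** Much can be said for the plan, and four stronger readings that a reader might infer do not hold.

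- **That the study will miss 20 EPV.** The plan covers 30–40%, and in the upper part of that range 1026 patients are enough for 16 coefficients. The shortfall belongs to the 30% planning value. Its size also depends on whether 1026 is before or after loss: the reference to the full sample, and the 12-month questionnaire as an inclusion criterion in Table 1, leave room for the milder figure of 19.2.
- **That the development set is frozen at 1026.** The following paragraph of the same section calculates the full required size after the prognostic value of the variables is known, and sets the temporal cut only then. The PREDICT section recalculates N if predictors are dropped or the prevalence differs, and inclusion stops only when the required size is reached.
- **That the 2370 total is undermined by 1026.** It is 2 × 1185, and the abstract and the PREDICT section agree on it.
- **That the article also plans for fifteen predictors.** The abstract's eleven and four add up to fifteen, but the abstract itself says sixteen. The slip is four where the body lists five.

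Two explanations remain inferences. The 14-predictor origin needs the × 1.1 allowance that Table 2 does not use. Items (8) and (10), both about medial malleolar height, and (9) and (11), talar curvature and convexity, may be the same measurements listed twice. The captions of Figs. 2–4 describe only seven measures, and the closing list of variables in the data-analysis section names each feature once. Against that, (10) and (11) are introduced as additional, cite a different source, and are said to lack the earlier evidence on instability claimed for the other items. The article does not settle it.

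Seventeen coefficients is also an upper case. Sixteen is called a maximum, one of a collinear pair is dropped, and only one of BMI and height is kept.

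What stands is that 1026 and 1185 are given for the same step, 1026 is not presented as a recalculated figure, and the recalculation has no single predictor count to start from.

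**Conclusion.** The figure of 1026 is wrong as written against the protocol's own 16-predictor plan. It is 159 below the required 1185 (1185 − 1026), a shortfall of about 13%. At 30% prevalence it yields 17.3 EPV with 10% lost or 19.2 with none lost, both under the stated minimum of 20. From about 34.7% or 31.2% prevalence respectively, the minimum would be met. These figures assume 16 coefficients; more coefficients would lower the EPV and fewer would raise it.

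The conflict between fourteen and sixteen predictors, with the related nine against eleven and four against five, is established by the text alone. The practical effect is a wrong fixed number in the main analysis section and an undefined input to the recalculation. The documents do not show a shortened recruitment target.

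**What to change.** 1. In the Prognostic model section under Data analysis and statistics, replace 1026 with 1185 or with a reference to the recalculated internal-validation sample size. Say whether the number is before or after loss to follow-up.
2. Give one list of distinct candidate predictors. State whether items (8) and (10), and (9) and (11), are different measurements; define each separately if so, and list it once if not. State whether MDTA enters as an angle or as classes.
3. Count regression coefficients as Table 2 defines them, with two for a three-level class, and recompute Table 2 once with division by 0.9.
4. Carry that count and N through the abstract, Clinical outcome measures, both Prognostic model sections, Assessment of agreement, Table 2 and PREDICT sample size, correcting fourteen, nine and four wherever they no longer fit.

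The cost is a correction of text and one table. If sixteen coefficients stand, the target remains 2370. If the agreed count is fourteen or seventeen, the two-phase total becomes 2 × 1038 = 2076 or 2 × 1260 = 2520, at 30% prevalence and 10% loss.

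### The analysis section sets the development sample at 1026 patients, against 1185 in the sample-size section, and nothing in the protocol derives 1026

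*Protocol article*

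**What the plan says.** Under Data analysis and statistics, Prognostic model, the protocol article states for internal validation that "apparent validation will be used, including the full sample size of 1026 patients". It gives no derivation.

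Under PREDICT sample size it states that "a sample size of 1185 patients is needed to perform the internal and 1185 patients is needed to perform the external model validation", for a total of 2370. That calculation is "Based on having maximally 16 variables with a minimum of 20 events per variable", with 30–40% prevalence and 10% loss to follow-up. The threshold is put as a requirement: "For a prognostic model at least 20 EPV is needed to optimize reliability and to avoid bias in regression coefficients".

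Table 2 shows the steps for 16 regression coefficients: "minimal 320 events", then "320*3.33 = 1065.6 patients" at 30% prevalence, then 889–1185 after the loss allowance.

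The number of predictors is not uniform. Under Analyses, Prognostic model, the text reads "This model is based on fourteen factors" and counts nine bone characteristics and five patient characteristics. Assessment of agreement speaks of fourteen variables in its first sentence and 16 in its second. Clinical outcome measures announces nine radiographic characteristics but numbers eleven, and with the five patient characteristics reaches 16.

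**The concern.** Two sections give different sizes for the same set of patients, the one on which the model is developed and internally validated. The figure in the analysis section is 13.4% lower (1 − 1026/1185), which is too much for rounding. It also sits beside the instructions for bootstrapping and validation, where an analyst would look for it.

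The plan justifies its size by a minimum of 20 events per variable. If 1026 were taken as the target, that minimum might not be reached under the plan's own design assumptions. It is also unclear whether 1026 means recruited or evaluable patients. This matters because the Missing data section excludes patients whose outcome cannot be determined or whose radiograph is missing.

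**Working it through.** **Inputs.** 16 coefficients, at least 20 events per variable, prevalence 30–40% and 10% loss (PREDICT sample size and Table 2); 1026 (Data analysis and statistics, Prognostic model); the competing count of 14 (Analyses, Prognostic model; Assessment of agreement).

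**Step 1: reproduce the plan's figure.** N = variables × events per variable / prevalence / (1 − loss).

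- 16 × 20 = 320 events; 320 / 0.30 / 0.90 = 1185.2, the stated 1185.
- At 40%: 320 / 0.40 / 0.90 = 888.9, the stated 889.
- At 10 events per variable: 160 / 0.30 / 0.90 = 592.6 and 160 / 0.40 / 0.90 = 444.4, the stated 593 and 445.

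Table 2 therefore divides by 0.90 for loss. Evaluable patients are 1185 × 0.90 = 1066.5, giving 1066.5 × 0.30 = 320 events.

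**Step 2: look for 1026 among the stated inputs.** With 16 variables at 30% prevalence:

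- loss as /0.90: 1184 to 1186, depending on rounding
- loss as ×1.10: 1172 to 1174
- no loss: 1066

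None of these is 1026. Nor is 1026 what remains of 1185 after the planned 10% loss; it would imply 13.4% loss.

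**Step 3: a possible origin.** 14 × 20 × 3.33 × 1.10 = 1025.6, which rounds to 1026. This needs 14 variables, Table 2's rounded multiplier 3.33, and a ×1.10 loss step that the protocol does not show. With an unrounded 1/0.30 the result is 1026.7. By the Table 2 method, 14 variables give 280 / 0.30 / 0.90 = 1037.0 (1036.0 with 3.33).

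**Step 4: events that 1026 would deliver.** Events = patients analysed × prevalence. If 1026 are recruited and 10% are lost, 1026 × 0.90 = 923.4 remain.

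| Reading | Prevalence | Events | Per variable, 16 | Per variable, 14 |
|---|---|---|---|---|
| 1026 analysed | 30% | 307.8 | 19.2 | 22.0 |
| 923 analysed | 30% | 277.0 | 17.3 | 19.8 |
| 1026 analysed | 40% | 410.4 | 25.7 | 29.3 |
| 923 analysed | 40% | 369.4 | 23.1 | 26.4 |

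**Step 5: break-even for 320 events.** 320 / 1026 = 31.2% prevalence if all 1026 are analysed; 320 / 923.4 = 34.7% if 10% are lost.

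**The case against.** The best defence is that 1026 is one stray figure. The abstract and the PREDICT sample size section agree on 2370, and Table 2 supports the 1185 behind it. The sample size is also to be recalculated if predictors drop out or prevalence differs, so 1026 may never govern anything. That limits the practical harm. It does not explain the figure, because the text presents 1026 as the full sample and ties it to no recalculation.

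A reader might go further in three ways that the document does not support.

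- **That 1026 is a 14-variable calculation with the loss allowance applied wrongly.** The surviving mentions of fourteen make a 14-variable origin plausible, but no section states it. Multiplication by 1.10 appears nowhere, so the protocol cannot be charged with that error.
- **That the model will miss 20 events per variable.** This holds for 16 coefficients when prevalence is below about 31% (1026 analysed) or 35% (1026 recruited, 10% lost). In the upper part of the plan's 30–40% range the minimum is met. It is also met at 30% with 14 variables if all 1026 are analysed. In the milder 16-variable case the gap is 12 events (320 − 307.8).
- **That the data will be cut at 1026.** The same section says the time stamp separating development from validation is chosen after the required size has been calculated and the time to reach it estimated. PREDICT sample size stops inclusion only at the required minimum.

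**Conclusion.** The contradiction stands: one section says 1026 and another 1185 for the same development set. Only 1185 follows from the stated inputs, so the figure in the analysis section is wrong as written.

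On the plan's own sizing assumptions (16 coefficients, 30% prevalence), 1026 yields 19.2 events per coefficient if all are analysed and 17.3 if 10% are lost, against a stated minimum of 20. The shortfall depends on those assumptions and is not certain. The 14-variable origin is probable but unproven, and the conclusion does not rest on it. Because a sample size the study relies on appears with two values, and correcting it costs almost nothing, it should be corrected before the development set is fixed.

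**What to change.** 1. Under Data analysis and statistics, Prognostic model, replace 1026 with the figure from PREDICT sample size. For example: all evaluable patients of the development set (1185 recruited, about 1066 evaluable after 10% loss, at least 320 CAI events), subject to the recalculation described there.
2. State one number of candidate predictors, 14 or 16, in Clinical outcome measures, in Prognostic model under Analyses, in Assessment of agreement and in PREDICT sample size.
3. Label every sample size as recruited or evaluable.
4. If 14 is meant, recalculate by the Table 2 method in every place: 280 / 0.30 / 0.90, about 1037 recruited per set.

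If 16 is kept, the cost is wording only and planned recruitment stays at 2370. If 14 is meant, Table 2 and the total must be restated, and the required number falls.
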